### Analyses

Baseline site and participant characteristics will be summarized descriptively. Patient outcomes will be summarized by group and site. Statistical analysis of the data will follow intention-to-treat principles. A linear mixed model will be used, with individuals’ data nested into a study site, to isolate the effect of the intervention on both clinical and process outcomes from other changes that may take place during the trial. Key contextual factors, such as patient’s sex and age, state of employment prior to stroke, stroke severity, concomitant rehabilitation treatments received outside the rehabilitation center, and time since stroke event (in days), will be considered in regression models as potential confounders. Interaction terms will be included in the model for any statistically significant contextual factors. Presence of dichotomous stroke outcomes (eg, dizziness) will be compared between study groups using a chi-square test. Multiple imputation will be considered if missing data represent more than 10% of a given variable. Sensitivity analysis will be conducted to assess the impact of missing data on estimates of intervention effects with a multiple imputation statistical technique and without imputation (ie, available case analyses), as well as for outlying observations.

Interviews and treatment plan meetings will be fully transcribed. A descriptive analytical approach will be used to develop a framework of organizational factors leading to a successful telerehabilitation intervention, both at the patient and professional levels. Audio recordings and transcripts will be reviewed simultaneously to assess validity of the transcription process and will be analyzed using an iterative approach [64]. Data saturation will be determined as defined by Constantinou et al [65]. This will be followed by an intersite analysis to identify what is common between the sites examined and what is specific to certain sites, and to compare the different configurations between sites. Finally, matrices with contextual factors will be generated to identify particular patterns [66].

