## Methods

### Study Design

An interrupted time series design with a convergent qualitative component is proposed to test the effectiveness of the intervention. The intervention consists of observing the same dependent variable over time, with a break in the series of observations corresponding to the introduction of an intervention. If the intervention is effective, a change in the series’ pre- and postintervention averages can be observed [45]. Moreover, such design will accommodate pre-existing trends and control for possible variations within and among sites (eg, rehabilitation treatment efficacy, low adherence to treatment plan, and team composition). This study was registered at ClinicalTrials.gov (NCT04440215).

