### Setting

Five selected sites in Quebec, Canada, will start with a control period (preintervention: usual care) until they independently reach their target sample size; this is expected to take between 12 and 18 months. Participants recruited during this period will belong to the control group. The sites will then enter the intervention period until recruitment completion, which is expected to occur after a further 12 to 18 months. Participants recruited during this second period will belong to the intervention group. Site monitoring will carefully document practices during both trial phases.

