### Sample Size Estimates

We calculated the sample size for a univariate comparison of the primary outcome between the two study groups at 12 weeks. The required sample size was calculated using G*Power (version 3.1.9.4; Heinrich-Heine-Universität Düsseldorf) based on a conservative estimated effect size of the intervention (Cohen *d*) of 0.4. This sample size was calculated assuming the following: (1) a two-sided type I error probability of 5% and a power of 80%, (2) a duration of 12 weeks, (3) a 2:1 ratio of intervention to control group participants, (4) two study groups, (5) a <5% loss to follow-up, and (6) intracluster correlations of 0.10. Therefore, 330 participants will be recruited: 110 and 220 participants in the control and intervention groups, respectively.

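### With site as the only nesting level, the before-after interval from five sites would be too narrow if sites shift differently between the two periods

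*Protocol article*

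**What the plan says.** The Analyses section specifies a linear mixed model with individuals' "data nested into a study site, to isolate the effect of the intervention on both clinical and process outcomes", and says that it separates this effect "from other changes that may take place during the trial". No level between patient and site is named. The Limitations section relies on the same model to avoid overstating the effect.

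The Setting section gives the design: "Five selected sites in Quebec, Canada, will start with a control period", and each site later moves to the intervention. For the control period, "this is expected to take between 12 and 18 months". The intervention period runs until recruitment is complete, "which is expected to occur after a further 12 to 18 months"; the Results section instead expects 2 to 3 years for it. On either figure, each period lasts about a year or more.

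The Study Design section says the design will "control for possible variations within and among sites (eg, rehabilitation treatment efficacy, low adherence to treatment plan, and team composition"). The Sample Size Estimates section gives one intracluster correlation, 0.10, with no between-period component.

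**The concern.** The intervention is switched on for whole sites, and every site contributes one before-after change. A site intercept removes what is constant about a site. It does not represent a site whose level moves between periods for reasons of its own, such as a changed team. Such a movement goes into that site's change and so into the estimated effect. A site-intercept model nevertheless judges the effect against patient-level residual variation only, with 330 − 5 − 1 = 324 residual degrees of freedom. The evidence about how much sites shift consists of five changes, which carry 4.

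At stake are the false-positive rate and the interval width. One or two atypical sites could make the result look significant, and the article intends its findings to inform practice guidelines.

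**Working it through.** **Inputs from the article.** Five sites (Setting). 110 control and 220 intervention patients, ICC 0.10, d = 0.4, two-sided 5%, 80% power, loss below 5% (Sample Size Estimates).

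**Assumptions not in the article.** Equal sites, so 110/5 = 22 and 220/5 = 44 patients. Total variance 1, so site variance is 0.10 and residual variance 0.90. The between-period correlation of a site's effect, r, is varied from 1 to 0.5.

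**The plan's own figure.** A two-sample t test with d = 0.4 and 2:1 allocation needs 75 + 150 = 225 patients, or 225/0.95 = 237 with loss. With 66 patients per site the usual design effect is 1 + 65 × 0.10 = 7.5, giving 225 × 7.5 ≈ 1,688 before loss. Using only the within-site factor 1 − 0.10 gives about 203. The one variant close to 330 takes the cluster size as 5: 225 × 1.4/0.95 ≈ 332. The article states no such cluster size. The 330 is therefore not reproduced from the stated inputs. What follows takes 110 and 220 as given and does not depend on this.

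**Step 1: standard error with a site intercept only.** The site effect cancels, leaving √[0.9 × (1/110 + 1/220)] = √0.01227 = 0.111 SD. When sites shift, the residual variance absorbs only a trace of it. At r = 0.8 it rises from 0.900 to 0.909, and the standard error stays at 0.111.

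**Step 2: true standard error.** The period-specific part of the site variance is 0.10 × (1 − r). It adds 2 × 0.10 × (1 − r)/5 to the variance of the effect, and more patients per site do not reduce it. At r = 0.8: 0.01227 + 0.008 = 0.02027, so the standard error is 0.142 and the ratio is 0.142/0.111 = 1.28.

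**Step 3: consequences.** Type I error is 2 × [1 − Φ(1.96/ratio)]. The site-level half-width is 2.776 × the true standard error (t on 4 df). Standard errors and half-widths are in SD units.

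| r | Site-only SE | True SE | Ratio | Site-only type I error | Half-width, site-only | Half-width, t(4) | Power t(4), d = 0.4 |
|---|---|---|---|---|---|---|---|
| 1 | 0.111 | 0.111 | 1.00 | 5.0% | 0.22 | 0.31 | 77% |
| 0.95 | 0.111 | 0.120 | 1.08 | 6.9% | 0.22 | 0.33 | 71% |
| 0.9 | 0.111 | 0.128 | 1.15 | 8.8% | 0.22 | 0.35 | 66% |
| 0.8 | 0.111 | 0.142 | 1.28 | 12.5% | 0.22 | 0.40 | 57% |
| 0.7 | 0.112 | 0.156 | 1.40 | 16% | 0.22 | 0.43 | 50% |
| 0.5 | 0.112 | 0.180 | 1.60 | 22% | 0.22 | 0.50 | 40% |

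**Step 4: simulation check.** Over 20,000 simulated trials per setting with no true effect, the within-site estimator rejected in 5.1%, 8.5%, 12.6%, 15.7% and 22.5% at r = 1, 0.9, 0.8, 0.7 and 0.5. A t test on the five site changes rejected in 4.7% to 5.1%. A REML random-intercept fit was run in batches of 300 and 1,200 trials. At r = 1 it rejected in 4.7% and 5.4% (pooled 79/1,500 = 5.3%). At r = 0.8 it rejected in 9.0% and 14.3% (pooled 199/1,500 = 13.3%).

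**Step 5: how well five sites estimate the added variance.** At r = 0.8 a single site's change has variance 0.9 × (1/22 + 1/44) + 2 × 0.02 = 0.0614 + 0.0400 = 0.1014. The site-by-period variance is estimated as zero when the observed variance of the five changes falls below about 0.0614. That probability is P(χ² on 4 df < 4 × 0.0614/0.1014 = 2.42) = 34%. At r = 0.9 it is P(χ² on 4 df < 4 × 0.0614/0.0814 = 3.02) = 45%.

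**The case against.** The article does not say that a random intercept is the only random effect. A model with a site-specific period effect also has patients nested in sites, and a condensed article may leave the random-effects structure and the degrees-of-freedom method to an analysis plan that is not shown. This stands as a limit on the finding: a reader might infer that the plan deliberately assumes no site-specific change, and the text does not show that. It does not remove the point. The article names one grouping level and claims that the resulting model isolates the effect from other changes, and that level alone does not deliver the claim for site-specific shifts.

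A reader might also infer that the interval is certainly too narrow. That depends on r being below 1, and the article gives no value; at r = 1 the site-only model holds 5%. Nor does the Study Design section list reasons why sites would drift apart. Of the plausible ones it names only team composition, and it speaks of variation within and among sites in general. Staff turnover is not mentioned anywhere. Service availability appears under Intervention Phase as a feature of each site, not as a change between periods. Adjustment for patient factors may also absorb shifts that come from case mix.

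Finally, an interval on 4 degrees of freedom is expensive even without drift. At r = 1, power for d = 0.4 falls from 95% with the site-only model to 77%. That is a fair reason not to make it the sole basis for the conclusion.

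**Conclusion.** The point holds in conditional form. If the model is fitted with a site intercept alone, its interval is too narrow whenever sites shift differently between periods: by a factor of 1.15 at r = 0.9, 1.28 at 0.8 and 1.60 at 0.5. The matching type I error is about 9%, 13% and 22% against a nominal 5%. These sizes rest on the article's ICC of 0.10 and on assumed equal sites of 22 + 44 patients. The range of r is an assumption too. Periods of a year or more, together with the article's own expectation of within-site variation, make r of exactly 1 hard to rely on, but they do not tell us its value.

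**What to change.** State the random-effects structure of the primary model: a random site effect plus a random site-by-period effect, with Kenward-Roger or equivalent small-sample degrees of freedom. As a supporting analysis, report the five site-specific changes with a site-level t interval on 4 degrees of freedom. The two belong together because the added variance is poorly estimated from five sites, and where it is estimated as zero the mixed model falls back to the site-only analysis. A rough balanced-data check still kept the mixed model's type I error near or below 5%. Restate power over a range of r, not at one value.

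The cost is analysis work, wider intervals and lower power; no extra data are needed. The Results section says analysis will not begin until data collection ends, so on that timetable the change can be prespecified. It does not remove bias from a trend shared by all five sites, which needs separate handling.

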## Results

As of July 2021, a total of 37 patients have been enrolled, from which 12 patients have completed the study. Data collection for the control group is expected to last for another 6 to 12 months; this will be completed before we begin the intervention group data collection, which should last 2 to 3 years. We do not intend to begin analysis before the end of the data collection period.

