### Limitations

Precautions will be taken to train each stroke team immediately prior to the intervention launch, to minimize contamination between the control and the intervention phases, which is one of the main risks of this study. The use of a linear mixed model should prevent an overestimation of the effect of the intervention [67], a common limitation of study designs that take place over a long period of time.

Another potential weakness is that organizational change entails an inner shift in the organization’s stakeholder values and aspirations as well as a series of behavior changes in response to external shifts in processes, strategies, and environments [68]. The proposed intervention will require adjustments from the rehabilitation professionals in order to gradually shift the teams’ ways of delivering care. Frequent scheduled interactions between rehabilitation and study teams should create an empowering context for the care providers involved in this trial; minimize anxiety, resistance, and unproductive behaviors; and ensure that the intervention implementation is rooted in the organization’s culture.

Findings from this study will inform best practices guidelines by providing empirical data on effective collaboration processes as well as optimized telerehabilitation delivery via telecare services. The production of a guideline called “How to better implement telerehabilitation within a stroke continuum” with dissemination through governmental agencies will aid sites not involved in this trial to implement telerehabilitation, in addition to classical dissemination, such as conferences and journal publications. This will also optimize the impacts of this intervention on stroke rehabilitation continuums beyond the trial sites.

This study represents a unique, highly relevant, and innovative opportunity to minimize both knowledge and practice gaps in rehabilitation stroke care, including interprofessional SDM. This study will produce robust data on the effectiveness of the intervention and in-depth data on the contextual factors and mechanisms that are related to its effectiveness, for whom and how. Participating health care providers will gain the wherewithal to engage patients and families and to develop their interprofessional decision-making skills, which are crucial to meet patients’ needs and significantly improve patient adherence.

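### The mixed model is credited with separating the intervention effect from change over time, but the analysis as described names no calendar-time, period or slope term

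*Protocol article*

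**What the plan says.** Three sections of the protocol article claim protection against change over time.

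- **Study Design** says of the interrupted time series that "such design will accommodate pre-existing trends and control for possible variations within and among sites". It describes an effective intervention as one that shifts the pre- and postintervention averages.
- **Analyses** names a linear mixed model, with individuals nested in study site, "to isolate the effect of the intervention on both clinical and process outcomes from other changes that may take place during the trial". The candidate confounders named are sex, age, prior employment, stroke severity, rehabilitation received outside the centre, and days since stroke. The list is introduced by 'such as'.
- **Limitations** states: "The use of a linear mixed model should prevent an overestimation of the effect of the intervention". It presents this as the answer to a common weakness of designs that run over a long period.

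On the order of the phases, **Setting** says that the five sites "will start with a control period (preintervention: usual care) until they independently reach their target sample size". It puts the length of this first phase at 12 to 18 months. Each site then enters the intervention period until recruitment ends, "which is expected to occur after a further 12 to 18 months". **Results** gives a longer intervention phase: control collection comes first, and "this will be completed before we begin the intervention group data collection, which should last 2 to 3 years".

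**Sample Size Estimates** sizes a univariate comparison of two groups at 12 weeks (d = 0.4, two-sided 5%, 80% power, 2:1, under 5% loss, intracluster correlation 0.10) and arrives at 110 + 220 = 330.

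**The concern.** Within every site, all control patients are enrolled before all intervention patients. Phase and calendar time are therefore strongly correlated, and only a model that contains time can separate them.

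A site effect compares patients with others at the same site, so it removes differences in level between sites. It does nothing about a site that changes between its first and second phase. Days since stroke is an interval belonging to the patient and does not stand in for the date of enrolment.

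Followed as written, the model yields a covariate-adjusted before-after difference. Gradual change in usual practice, staffing or the completeness of exercise journals would be counted as intervention effect if it raises recorded minutes, and would hide a real effect if it lowers them. This is the main threat to a design with one switch per site, and the article tells the reader that it has been dealt with.

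**Working it through.** **1. The plan's own figure.** The control-group size for d = 0.4 at 2:1 is (1 + 1/2) × (1.96 + 0.842)² / 0.4² = 73.6, so 74 + 148 = 222 (exact t test: 75 + 150 = 225). Multiplying by a design effect of 1 + (5 − 1) × 0.10 = 1.4 and dividing by 0.95 gives 327.2, so 328 (t test: 332). That is close to the stated 330. It requires a cluster size of 5, which the article does not state. No step allows for a time term.

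**2. Bias without a time term.** With even accrual and linear drift, spurious effect = drift × gap between mean enrolment dates, and gap = (control length + intervention length) / 2. The drift rates are assumptions; the article gives none.

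For the false-positive rate, take 5% loss (104.5 and 209 patients) and within-site variance 1 − 0.10 = 0.9. Then SE = √[0.9 × (1/104.5 + 1/209)] = 0.114, and the rate is P(|Z + bias/SE| > 1.96).

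| Control + intervention (years) | Gap (years) | Drift (SD/year) | Spurious effect (SD) | Share of 0.4 | False-positive rate |
|---|---|---|---|---|---|
| 1.25 + 1.25 | 1.25 | 0.05 | 0.0625 | 16% | 8.5% |
| 1.25 + 1.25 | 1.25 | 0.10 | 0.125 | 31% | 19.6% |
| 1.25 + 1.25 | 1.25 | 0.20 | 0.25 | 62.5% | 59.5% |
| 2 + 3 | 2.5 | 0.05 | 0.125 | 31% | 19.6% |
| 2 + 3 | 2.5 | 0.10 | 0.25 | 62.5% | 59.5% |
| 2 + 3 | 2.5 | 0.20 | 0.50 | 125% | 99.3% |

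The first three rows use the middle of the range in Setting. The last three use the upper end of the intervention length in Results, with an assumed two-year control phase. A simulation with five sites, 330 patients, intracluster correlation 0.10 and phases of 12 to 18 months gave 7.8%, 20.9% and 62.4% for the first three rows.

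The bias does not depend on the SE, but the false-positive rate does. If the SE carried the design effect of 1.4, it would be √(1.4 × 0.01435) = 0.142, and those three rates would be 7%, 14% and 42%.

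**3. Effect of adding linear enrolment time.** In the same simulation, the mean estimate under no effect returned to about 0.00 and the false-positive rate to 4–5%, at every drift rate.

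**4. Price in precision.** Variance inflation = 1 + (between-phase variance of time) / (within-phase variance of time), with two-thirds of patients in the intervention phase.

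- Phases of 1.25 + 1.25 years: between = (2/9) × 1.25² = 0.347; within = 1.25²/12 = 0.130; inflation = 3.67.
- Phases of 1.5 + 3 years: between = (2/9) × 2.25² = 1.125; within = (1.5²/3 + 2 × 3²/3)/12 = 0.5625; inflation = 3.00.

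Power = Φ(0.4/SE − 1.96), with SE² = 0.01435 × design effect × inflation:

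| Design effect | No time term | Inflation 3.67 | Inflation 3.00 |
|---|---|---|---|
| 1.4 (reproduces 330) | 80.6% | 31% | 37% |
| 1 | 91.6% | 41% | 49% |

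Restoring 80% power would need 222 × inflation / 0.95 patients, about 702 to 858, or about 982 to 1,201 with the design effect of 1.4.

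**The case against.** The strongest reply is that this is a condensed article. It never lists the model's terms in full, and the covariate list is open. Naming the design an interrupted time series is consistent with a time term being intended. A reader might infer that the model excludes calendar time; the documents do not support that, and the exact statement is that no such term is named.

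Nor do the remark about averages in Study Design and the univariate sizing prove that the final model is a bare difference in means. The first is a general description of the design, and sizing on a simpler test is common. The source cited for the Limitations claim is not at hand.

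Other limits also stand:

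- A reader might infer that any secular trend would be reported as an intervention benefit. That goes too far. Case-mix drift captured by severity, time since stroke or outside rehabilitation would be adjusted away if those covariates enter the model, and the remaining bias can run in either direction.
- Site monitoring is to document practice in both phases. It would help interpretation but does not adjust the estimate.
- No drift rate can be drawn from the documents, so no single false-positive figure should be quoted as a fact about this trial.
- Staggered switch dates should not be relied on. Setting has sites reach their targets independently, while Results can be read as all control collection finishing first. Staggering would not help in any case without time in the model.

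What the reply does not rescue are the claims themselves. The article does more than leave a detail open: it attributes control of change over time to nesting and to the use of a mixed model, and neither provides it.

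**Conclusion.** The point holds in this form: the analysis as described lacks the property claimed for it in Study Design, Analyses and Limitations. Drift not explained by the listed covariates would pass into the phase effect.

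On 15-month phases the distortion runs from about 0.06 to 0.25 SD across assumed drifts of 0.05 to 0.20 SD per year. It is larger on the timeline in Results, because the gap between phases is longer. These sizes rest on linear drift, even accrual and equal sites. They show what the model leaves exposed and do not predict what will happen.

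The stated 80% power applies only to the comparison without a time term. With 330 patients the trial can offer that comparison at about the planned power, or a trend-adjusted estimate at roughly 31–49% power. The text currently promises the protection of the second at the power of the first.

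**What to change.** **Preferred.** In Analyses, name enrolment time (months from the site's switch, with a linear slope common to all sites) as a fixed effect in the mixed model. Define the intervention effect as the level change at the switch, and report the unadjusted before-after difference alongside it. State in Sample Size Estimates that the 80% refers to the comparison without a time term, and give the power with it.

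**Alternative.** If the primary model stays without a time term, remove the trend-control claims from Study Design, Analyses and Limitations. Describe the result as an uncontrolled before-after difference, and prespecify the time-adjusted estimate as a sensitivity analysis.

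**Cost.** The change needs one model term and the enrolment dates, which should exist for every consented patient. The real cost is precision: the 3.0- to 3.7-fold variance inflation and loss of power shown above. A linear term also removes only linear drift. The choice can still be made before outcomes are examined: Results reports 37 patients enrolled as of July 2021, with the control phase still open and no analysis intended until data collection ends.

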### Primary Outcome

The choice of the primary outcome, patient adherence to the stroke rehabilitation plan at 12 weeks, was identified through a pilot study previously conducted by our research team as the most meaningful outcome and to better document the reason why telerehabilitation might be effective. Adherence to telerehabilitation has been operationalized in many different ways across studies [6,51]. We will define adherence as time spent (in minutes) doing any stroke rehabilitation exercises (online + offline). This includes, but is not limited to, physical, writing, and speech therapy as well as mental health–related exercises recommended by the rehabilitation professional. Online session time will be recorded through the telerehabilitation platform. Offline time will include face-to-face sessions doing rehabilitation as well as time exercising on one’s own as instructed by the rehabilitation professional. Offline sessions completed at home will be captured with the use of a journal and recorded by one of the rehabilitation professionals each week. This monitoring step has been used as a method of quality assurance by other scholars in stroke research [52]. Patients’ adherence to a rehabilitation program will also be measured by the Stroke Rehabilitation Exercise Adherence Measure (StREAM) questionnaire at weeks 4, 6 (to allow for test-retest reliability assessment), and 12 [53]. Moreover, health care professional perception of the participants’ adherence to the rehabilitation program will be evaluated on a numerical 10-point rating scale each week during the intervention period.

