**Patients**			
	Reintegration into normal life	Reintegration to Normal Living Index [54]	Baseline and 12 weeks
	Ability to perform daily activities	Functional Independence Measure [46]	Baseline and 12 weeks
	Participation in shared decision making (SDM)	Questionnaire by Strull et al [55]	Following the establishment of the patient treatment plan
	Decisional conflict	SURE (Sure of myself; Understand information; Risk-benefit ratio; Encouragement) questionnaire [56]	Following the establishment of the patient treatment plan
	Satisfaction with treatment plan	Satisfaction with Decision scale [57]	Following the establishment of the patient treatment plan
	Depression	The Beck Depression Inventory [58]	Baseline, 12 weeks, and 24 weeks
	Satisfaction with health care received	Health Care Satisfaction Questionnaire [59]	12 weeks

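### Rehabilitation received elsewhere during treatment is listed as a confounder; adjusting for it would no longer estimate the total effect of the intervention

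*Protocol article*

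**What the plan says.** Methods, Analyses, plans a linear mixed model with patients nested in sites, analysed by intention to treat. Its purpose is to separate the intervention effect from other changes during the trial. An open list of contextual factors follows: sex, age, employment before the stroke, stroke severity, and then "concomitant rehabilitation treatments received outside the rehabilitation center, and time since stroke event (in days), will be considered in regression models as potential confounders". The next sentence adds interaction terms for any of these factors that turns out significant.

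Methods, Primary Outcome, defines adherence as minutes spent "doing any stroke rehabilitation exercises (online + offline". Offline time includes face-to-face sessions and independent exercise. The section does not say whether sessions given by providers outside the study centre are counted.

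Methods, Setting, forms the groups by recruitment period: usual care first, then the intervention, at each of five sites.

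**The concern.** Sex, age, prior employment, stroke severity and time since stroke are naturally fixed before treatment. Outside rehabilitation is described as concomitant, which most naturally means that it takes place during study treatment. The intervention could alter it. Telerehabilitation is meant to reduce travel (Discussion, Impact), and the care plan is agreed jointly with the patient (Methods, Intervention Phase). The article itself treats use of services as an outcome (Abstract, Objective; Table 1, health care use at 12 and 24 weeks).

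A variable that the intervention can change is not a confounder of the intervention's total effect. Holding it constant removes whatever part of the effect passes through it. If a patient's motivation, for example, drives both outside care and exercise minutes, conditioning on outside care can also create a spurious association between group and outcome. If outside minutes are counted, the model would in addition adjust the outcome for one of its own components. What is at stake is the meaning of the main adherence estimate.

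**Working it through.** **Inputs from the article (Sample Size Estimates).** The planning effect is a "conservative estimated effect size of the intervention (Cohen *d*) of 0.4". Group sizes are 110 control and 220 intervention.

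**Inputs not in the article, assumed.** ρ, the within-group correlation of outside rehabilitation with the outcome, is taken as 0.2 to 0.6. d_O, the intervention-minus-control difference in outside rehabilitation in SD units, is taken as −0.4 to +0.4.

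**Step 1: the plan's own figure.** This point contests no number; the planning effect only sets the scale. With two-sided 5%, 80% power and "a 2:1 ratio of intervention to control group participants", the control group needs 1.5 × (1.960 + 0.842)² / 0.4² = 73.6, so 74, and 222 in total. A design effect of 1 + (5 − 1) × 0.10 = 1.4 and 5% loss give 74 × 1.4 / 0.95 = 109.05, so 110 control and 330 in total, as stated. Whether 5, the number of sites, is the right cluster size is a separate matter and is not used below.

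**Step 2: formula.** In a least-squares model with group and outside rehabilitation, both variables scaled to their within-group SD:

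adjusted effect = d_Y − ρ × d_O

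where d_Y is the total effect. The shift does not depend on why the two variables are correlated within groups.

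**Step 3: numbers, with d_Y = 0.40.**

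| ρ | d_O = −0.4 | −0.2 | 0 | +0.2 | +0.4 |
|---|---|---|---|---|---|
| 0.2 | 0.48 | 0.44 | 0.40 | 0.36 | 0.32 |
| 0.4 | 0.56 | 0.48 | 0.40 | 0.32 | 0.24 |
| 0.6 | 0.64 | 0.52 | 0.40 | 0.28 | 0.16 |

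For example, 0.40 − 0.6 × (−0.4) = 0.64 and 0.40 − 0.6 × 0.4 = 0.16. If the intervention lowers outside use, the adjusted estimate is too high; if it raises outside use, too low. A simulation with 110 and 220 patients and 400 runs per cell gave means within 0.01 of every entry.

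**Step 4: interaction rule.** A covariate that may overlap the outcome is likely to be significant, so the rule could well bring in its interaction, presumably with group. The group coefficient would then be the effect at one chosen level of a post-treatment variable, further still from a total effect.

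**Step 5: baseline scores (for the recommendation only).** A baseline score with correlation r to its own 12-week value multiplies residual variance by 1 − r²: 0.91, 0.75 and 0.51 for assumed r of 0.3, 0.5 and 0.7. This applies to outcomes with a baseline value. Adherence minutes have none.

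**The case against.** The strongest defence concerns the design. Recruitment runs over years and groups are formed by period, so access to outside care may drift for reasons unrelated to the intervention. In that case outside care is partly a co-intervention that differs by period, and leaving it out lets the drift into the estimate. This stands, and it is why the variable belongs in a sensitivity analysis and should not simply be dropped. It does not make a variable measured during treatment a sound covariate for the main estimate: the model cannot tell drift from an effect of the intervention. Use before enrolment, if known, could be adjusted for safely.

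It can also be said that the factors are only to be considered and that the full covariate set belongs in the analysis plan. But the unsuitable variable is named in the text, so this is not a missing detail, and leaving its use optional adds discretion without removing the problem.

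Three stronger readings are tempting, and the article supports none of them:

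- **Outside rehabilitation is part of the primary outcome.** The word *any* points that way. However, the same section describes exercises recommended by the rehabilitation professional, captured by a platform log and a home journal. Outside sessions are neither included nor excluded.
- **The adjusted estimate will be too favourable.** If outside use fell from 30% to 15% and users logged 0.5 SD more minutes, the estimate would rise by 0.15 × 0.5 = 0.075 SD, or 19% of 0.4. That is one assumed scenario. The article says nothing about home access replacing other care, and the direction could reverse.
- **Baseline scores are left out of the models.** Table 1 schedules baseline measurement for reintegration, function and depression (the last at "Baseline, 12 weeks, and 24 weeks"), and none is named in Analyses. But the list is open, it already includes stroke severity, and a mixed model can carry baseline as a repeated measure.

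**Conclusion.** The point holds in a limited form. The article names as a potential confounder a variable that is concurrent with treatment and open to change by the intervention. Adjusting for it, or interacting it with group, conflicts with estimating the total effect by intention to treat. This is so whether or not outside minutes are counted; if they are, the problem is worse.

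The size is unknown. Under the assumed ranges a total effect of 0.40 would be estimated as 0.16 to 0.64. That range takes the whole group difference in outside use to be caused by the intervention. To the extent that the difference reflects calendar drift, adjustment may remove real confounding. With no group difference in outside use there is no shift.

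**What to change.** 1. Restrict the covariates and interaction terms of the main model to variables fixed before treatment starts. Outside rehabilitation before enrolment may be included if it is known.
2. Report outside rehabilitation during follow-up by group, and adjust for it only in a labelled sensitivity analysis.
3. State whether minutes of outside rehabilitation count in the primary outcome.

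As a recommendation only: name the baseline score of the same instrument as a covariate in the reintegration, function and depression models. The gain in precision applies to those secondary outcomes, not to adherence minutes.

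The cost is wording. The baseline scores are already scheduled, and the Results section says that analysis will not begin before data collection ends, so the change can be fixed in advance of analysis. The small downside is that a change over calendar time in outside care, unrelated to the intervention, is then addressed only in the sensitivity analysis.
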